**Double-centre, prospective, controlled, longitudinal open study**

**Research Plan**

# A. Introduction

## 1. Objective

Bariatric operations such as the gastric bypass procedure provide a unique *in vivo* model of improvement of pathological beta cell function. The presented double-centre study aims to comprehensively investigate different aspects of beta cell function in patients with type 2 diabetes (T2DM) with a wide range of disease duration after gastric bypass. In parallel, our project will address the aspects of changes in enteroinsular and adipoinsular axes as well as the early and late changes of other defined parameters after gastric bypass surgery.

## 2. Background and current status of research in the proposed field of the study

Epidemiological evidence confirms that weight loss significantly decreases the risk for development of type 2 diabetes [1]. Morbid obesity per se is associated with profound insulin resistance and subsequent hypersecretion of insulin but the dynamics of beta cell function are still preserved [2]. On the other hand, overt diabetes is characterized by a progressive loss of beta cell glucose sensitivity [3]. In contrast to traditional weight reduction treatments, bariatric surgery has been proven not only to induce a sustained long-term weight loss but also to resolve type 2 diabetes in the majority of patients and it therefore represents an interesting model of weight loss and related changes in glucose metabolism [4]. However, resolution rates of diabetes after bariatric surgery clearly depend on the specific type of operation rather than on the amount of weight loss per se [5]. Bilio-pancreatic diversion (BPD) has consistently been found to show the highest remission rate (i.e. about 99%) followed by Roux-en-Y gastric bypass (85%), whereas purely restrictive procedures such as gastroplasty and gastric banding induce lower rates of diabetes resolution (72% and 48%; respectively). Together these findings point to distinct influences of different surgical procedures on glucose metabolism with those excluding the duodenum from the passage and enhancing the delivery of nutrients to the hindgut being the most effective.

Remarkably, in many cases the beneficial effect of bariatric surgery on glucose metabolism occurs within days after surgery, i.e. even before a significant weight loss has been achieved. However, in other cases glucose metabolism only gradually improved in parallel with the progression of weight loss until a complete remission has been achieved [6-8]. Observational clinical studies suggest that the chance of recovery from T2DM due to surgery decreases with increasing duration of the disease [9]. Though, surgery-induced remission of T2DM is also not uncommon in patients with long standing diabetes. Thus, strong predictors for the course of T2DM after gastric bypass surgery are still lacking which may result from insufficient preoperative metabolic characterisation of T2DM patients in many foregoing observational studies.

Mechanisms which lead to a resolution of T2DM following BDP and gastric bypass surgery are incompletely understood yet. A substantial improvement of insulin sensitivity and a decrease in absolute insulin secretion in combination with improvement of beta cell glucose sensitivity have been shown in previous studies [10, 11] The improvement of insulin sensitivity has been attributed to an enhanced insulin signalling in muscle [12] and changed expression of genes regulating glucose and lipid metabolism [13] within skeletal muscle tissue along with a depletion of intramyocellular fat stores [14].

In regard to beta cell function it has been shown that glucose sensitivity assessed by an oral glucose tolerance test (OGTT) markedly improved within one week after a BPD operation [10, 15] and that this improvement continued over a period of at least two years [16]. The improvement of beta cell function has been attributed to enhanced secretion of incretins, especially glucagon-like peptide-1 (GLP-1), and also to reduced release of yet to be identified anti-incretins resulting from the exclusion of the nutrient flow through the proximal intestine [17, 18]. However, several studies [19-21] have also demonstrated a restoration of the acute insulin response (AIR) during an intravenous glucose tolerance test (IVGTT) in T2DM patients early after a BPD operation. This finding suggests that enhanced incretin secretion does not represent the only mechanism underlying the improvement of beta cell function because the release of incretins critically relies on the passage of glucose through the gastrointestinal tract that is not given during an IVGTT. In addition, a reduction of lipotoxicity has been proposed as another mechanism contributing to the improvement of beta cell function after surgery [20]. However it should also be noted that all of the above mentioned results on beta cell function are derived from studies examining the effects of BPD not gastric bypass procedures. Of note, BPD operations in contrast to the standard proximal gastric bypass procedure lead to a strong lipid malabsorption which may result in an especially pronounced reduction of beta cell lipotoxicity. Overall, it is not even clear yet whether the AIR to an intravenous glucose challenge is recovered in T2DM patients after gastric bypass surgery and thus, whether the improvement of beta cell function relies on mechanisms not depending on an enhanced release of incretin hormones [22, 23]. This question appears to be of particular importance when considering that gastric bypass represents a far more popular bariatric procedure than the BPD [24].

Besides above discussed mechanisms, changes of adipokines and inflammatory mediators from adipose tissue have been postulated to be responsible for long-term improvement in glucose metabolism after gastric bypass in relation to reduced fat mass [25]. The role of adipose-tissue derived factors in insulin resistance is widely acknowledged [26], however their relation to beta cell function is not clarified yet. Based on cell culture experiments and rodent models, experimental evidence exists that adipokines and inflammatory mediators directly interact with beta cell function through regulation of lipid and glucose metabolism in the beta cell (leptin, free fatty acids), through changes in insulin secretion (leptin, TNFα, adiponectin, free fatty acids, IL6), changes in insulin gene expression (leptin), or through modification of beta cell glucose and insulin sensitivity or beta cell apoptosis (leptin, adiponectin, IL6, TNFα) [27, 28]. An inflammatory process in islets from patients with T2DM as a response to metabolic stress with activation of the IL-1β pathway has been recently postulated to contribute to beta cell failure and enhanced apoptosis [29].

Clinical data supporting causal relationships within the adipoinsular axis are still lacking. Changes in beta cell function after bariatric surgery therefore represent a useful clinical model for investigation of adipoinsular axis. However, clinical studies dealing with changes of adipokines after bariatric surgery did not address beta cell function in parallel, and vice versa.

Plasma concentrations of leptin are consistently reported to decrease after bariatric surgery, already within 4 weeks [10, 30-32], its decline reflects long-term BMI reduction [31], but the correlation of leptin with beta cell function improvement was rarely investigated and the results are conflicting – there are both pros [10, 33] and contras [20]. An increase in plasma adiponectin after bariatric surgery is consistently found in the literature [32, 34-36], but again the relation to beta cell function has been rarely investigated with contradictory results [20, 33]. Similarly, other adipose-tissue derived cytokines and inflammatory factors (TNFα, IL6, MCP-1, hs-CRP, IL-1ra [receptor antagonist for IL1β], IL10) implicated in chronic low-grade inflammation associated with obesity, have been previously assessed after bariatric surgery [30, 37-39], but were never related to beta cell function.

Additionally, most of the above mentioned studies used to determine only circulating concentrations of adipokines and inflammatory mediators. Changes in adipose-tissue derived factors at the tissue level (mRNA expressions) in comparison with controls were not systematically investigated yet.

Moreover, differential responses of adipoinsular axis to bariatric surgery in relation to diabetic status have not been elucidated so far, the indices in literature are based on small numbers of patients included in the study [40] and need further evaluation.

Besides the serious limitations on the mechanistic knowledge of beta cell function recovery after bariatric surgery outlined above, it must be emphasized that the available experimental data on this issue almost exclusively derive from patients with a rather short duration of T2DM (< 6 years). On this background, the question arises whether surgery induced beta cell function improvement also occurs after longer duration of the disease which is expected to be associated with aggravated beta cell damage. Such an improvement would dramatically challenge the traditional view of an irreversible damage to beta cells in long standing T2DM.

# Specific Aims

## Zero hypothesis: There is no difference in terms of beta cell function in patients with short- and long-term history of T2DM following gastric bypass.

## Alternative hypothesis: There is a significant difference in terms of beta cell function in patients with short- and long-term history of T2DM following gastric bypass.

**Primary objective**:

Comparison of the changes in beta cell function following gastric bypass in patients with short- and long-term history of T2DM

**Primary outcome variable**:

Acute insulin response (AIR) to glucose during IVGTT will be used as a primary variable characterizing the beta cell function.

**Secondary objectives:**

- - - Assessment of the beta cell insulin response to oral and intravenous glucose loads early and 1 year after gastric bypass surgery including the quantification of the incretin effect using oral and isoglycaemic intravenous glucose infusion tests
    - Relation of early and long-term changes in beta cell function to changes in parameters of adipoinsular and enteroinsular axes in severely obese patients with and without T2DM
    - Comparison of the changes in adipoinsular and enteroinsular axes after weight loss achieved after gastric bypass with BMI-matched non-bariatric controls

**Secondary outcome variables**:

- OGTT calculations and modelling describing beta cell response to oral glucose load (see paragraph D.5. Calculations, page 7); Insulin and C-peptide areas under the curve (AUCs) during OGTT and isoglycaemic iv. glucose infusion quantifying the incretin effect.
- Plasma concentrations and adipose tissue expression of selected adipokines and inflammatory cytokines characterizing the adipoinsular axis
- Plasma concentrations of incretins GLP-1 and GIP and their time profiles during OGTT and isoglycaemic iv. glucose infusion.

# Preliminary data

*Study group justification*

In St. Gallen, approximately 160 patients per year undergo gastric bypass surgery, of which about 30% display T2DM. Thus, it is expected to ensure the recruitment of 40 T2DM patients and 15 non-diabetic patients over 1 year. In Graz, approximately 60 patients per year are submitted for gastric bypass surgery, a third of them displaying T2DM. Expecting the recruitment of 15 T2DM patients and 15 non-diabetic (non-DM) patients per year in Graz, the total number of surgery patients included in the study is 85 patients (55 T2DM, 30 non-DM). A drop-out rate during follow-up is estimated for 10-12%.

*Publications regarding gastric bypass and glucose metabolism – St. Gallen*

The applicant from St. Gallen has a 3.5 years experience in the clinical management of morbid obese patients undergoing bariatric surgery. He has published on several nutritional aspects bariatric surgery [41-43]. Furthermore, he has extensive experience in performing experimental clinical studies on glucose metabolism with a special focus of hypoglycemia counterregulation [44-49].

*Established analysis of cytokines, hormones, gene expression – Graz*

Medical University of Graz disposes of established laboratorial facilities which have validated the methods applied in the presented study. The multiplex flow-cytometric bead based ELISA assay (LUMINEX) has been introduced and validated for multiple measurements of small sample volumes and published in previous studies [50-53]. The immunochemical analysis of endocrine and metabolic parameters (ELISA, RIA, LIA) is available both for routine and research purposes, as well as the gene expression analysis via real-time PCR documented by several publication [54-60]

# Methodology

## Population

Bariatric group: 85 severely obese patients (55 T2DM patients and 30 non-diabetic [non-DM] patients) fulfilling the indication criteria for laparoscopic gastric bypass surgery including the personal wish to undergo gastric bypass will be consecutively recruited at the Obesity Outpatient Clinic, Medical University Graz, Austria and at Interdisciplinary Obesity Center in St. Gallen, Switzerland. In the subgroup of T2DM surgery patients, patients with wide range of disease duration will be included. Long-standing T2DM will be classified as the disease duration longer than 10 years at the time of surgery. Within the T2DM subgroup, the expected proportion of long-standing T2DM will be 40-50%. For the detailed recruitment proportions at both sites see Table 1.

Control group: 30 patients (15 T2DM patients and 15 non-DM patients) undergoing elective laparoscopic abdominal surgery in the absence of neoplastic disease, acute or chronic inflammatory disease will be consecutively recruited at both sites. The control group will be matched with bariatric group for age, sex and expected one-year postoperative BMI (BMI 27-35 kg/m^2^).

| Site | **Bariatric group (n=85)** | | **Control group (n=30)**  **(15 T2DM / 15 non-DM)** |
| --- | --- | --- | --- |
|  | **T2DM** | **non-DM** |  |
| Graz, Austria | 15 | 15 | 15 |
| St. Gallen, Switzerland | 40 | 15 | 15 |
| Total | 55 | 30 | 30 |

*Table 1. Recruitment proportions at both sites.*

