## 6. Statistical analysis

All data will be checked for distribution normality. In case of non-Gaussian distribution, log transformed data will be assured for further statistical evaluation.

1. Changes in beta cell function and other variables after gastric bypass surgery will be assessed by analysis of variance (ANOVA) with repeated measures. ANOVA models will include following factors:
   1. group factor as the between-subject factor (comparison between groups of bariatric patients with short- and long-standing T2DM and bariatric patients without T2DM)
   2. time factor (repeated measurements at baseline and two follow-up visits)
   3. treatment factor if appropriate - in case of repeated measurements within 1 follow-up (eg. GLP-1 profile during OGTT, basal + insulin-stimulated concentrations of adipokines and cytokines)

Time and treatment factors as the within-subject factors account for the repetition in the ANOVA model.

1. Relations between changes in beta cell function and clinical characteristics or changes in parameters of adipoinsular and enteroinsular axes will be evaluated using multivariate regression analyses.
2. For comparison of beta cell function and other variables after weight loss achieved following gastric bypass with results from BMI-matched non-bariatric controls, Mann-Whitney *U* test will be used.

Based of foregoing studies [10, 11, 19-21] a sample size of at least 15 subjects per subgroup can be safely expected to provide a sufficient statistical power to detect meaningful changes in beta cell function. Our sample size is based on feasible recruitment expectations at both sites: total number of 85 patients with an estimated drop-out rate of 10-12% during the follow-up, giving the final sample size of 75 patients – 50 patients with T2DM (among them approx. 40-50% with long-standing T2DM) and 25 patients without T2DM.

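### Non-diabetic bypass patients are neither matched to nor paced with the T2DM bypass patients, and the planned ANOVA lists no site, age, sex or BMI term, so the secondary T2DM versus non-DM contrasts may be confounded

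*Protocol*

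**What the plan says.** **Recruitment.** Under Methodology, Population, bypass patients "fulfilling the indication criteria for laparoscopic gastric bypass surgery including the personal wish to undergo gastric bypass will be consecutively recruited". Table 1 fixes the places: T2DM 40 at St. Gallen and 15 at Graz, non-DM 15 at each site.

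**Matching.** The one matching rule covers the 30 non-bariatric surgical controls: "The control group will be matched with bariatric group for age, sex and expected one-year postoperative BMI". No such rule links the non-DM bypass patients to the T2DM bypass patients.

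**Volumes.** Under Preliminary data, St. Gallen reports "approximately 160 patients per year undergo gastric bypass surgery, of which about 30% display T2DM", and at Graz "approximately 60 patients per year are submitted for gastric bypass surgery, a third of them displaying T2DM". For St. Gallen the expectation is "recruitment of 40 T2DM patients and 15 non-diabetic patients over 1 year"; for Graz it is 15 and 15 per year.

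**Analysis.** In section 6 the between-subject factor of the repeated-measures ANOVA is a "comparison between groups of bariatric patients with short- and long-standing T2DM and bariatric patients without T2DM". The other listed factors are time and, where appropriate, treatment. A separate multivariate regression relates changes in beta cell function to clinical characteristics and to the hormonal axes. One secondary objective concerns such relations "in severely obese patients with and without T2DM".

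**The concern.** T2DM and non-DM bypass patients are not randomised, so a difference between them can reflect anything else in which the groups differ. The protocol treats age, sex and BMI as needing control when it chooses the surgical controls, but leaves them free in the contrast by diabetes status within the bypass group.

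That contrast is a stated use of the data. Non-DM patients are a level of the ANOVA group factor, and the Background calls the differential adipoinsular response by diabetic status an open question. If site, age, sex, BMI or enrolment period differs between the groups and also affects the outcome, its effect would be reported as an effect of diabetes. A later analysis plan can add covariates, but it cannot change who was enrolled or when.

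**Working it through.** **The plan's own figures.** Section 6 expects 75 completers of 85 after 10-12% drop-out: 85 × 0.90 = 76.5 and 85 × 0.88 = 74.8, which fits 75 (50 T2DM, 25 non-DM). The Table 1 totals also agree: 40 + 15 = 55 and 15 + 15 = 30.

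**Candidates and time to fill.** Candidates per year = site volume × share with or without T2DM. Weeks to fill = places / (candidates × participation) × 52.

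| | T2DM, St. Gallen | T2DM, Graz | non-DM, St. Gallen | non-DM, Graz |
|---|---|---|---|---|
| Candidates per year | 160 × 0.30 = 48 | 60 × 1/3 = 20 | 160 × 0.70 = 112 | 60 × 2/3 = 40 |
| Places | 40 | 15 | 15 | 15 |
| Share needed in one year | 83% | 75% | 13% | 38% |
| Weeks, full participation | 43 | 39 | 7 | 19.5 |
| Weeks, 50% participation | 87 | 78 | 14 | 39 |

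The non-DM pool is 112 + 40 = 152 a year for 30 places (5.1 to 1). The T2DM pool is 48 + 20 = 68 for 55 places (81% needed). If non-DM patients also took part at 81%, about 123 would remain (4.1 to 1).

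**Overlap in time.** If participation is the same in both groups, whatever its level, the T2DM patients enrolled while non-DM places are open number 48 × 15/112 = 6.4 of 40 at St. Gallen and 20 × 15/40 = 7.5 of 15 at Graz. That is about 14 of 55, or 25%. The gap closes only if non-DM participation is much lower, near 13% at St. Gallen and 38% at Graz.

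**Site.** Graz share: 15/55 = 27% of T2DM and 15/30 = 50% of non-DM patients, a difference of 0.23. If an outcome (or its change) differs between sites by δ, the unadjusted contrast shifts by 0.23 × δ. For an assumed δ of 0.5 or 1 SD this is 0.11 or 0.23 SD. The protocol gives no value for δ.

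**What matching could achieve.** The protocol gives no age, sex or BMI by diabetes status, so the starting imbalance is an assumption. In a simulation (500 runs per setting, two normal covariates, nearest-neighbour matching within site), differences of 0.3, 0.5 and 0.8 SD remained in full without matching. They fell to about 0.05, 0.09 and 0.19 SD when the full pool was available, and to 0.11, 0.20 and 0.36 SD with half of it. Matching in broad bands as patients arrive would be expected to achieve somewhat less.

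**The case against.** Several points on the other side stand.

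- A reader might infer that consecutive recruitment and 15 non-DM patients over one year at St. Gallen contradict each other. They do not. The one-year statement is a feasibility expectation that sets no pace: early filling satisfies it, and participation near 13% would reconcile the two literally. The visit schedule is demanding and no non-DM participation rate is given.
- A reader might infer that age, sex or BMI imbalance is present. Nothing in the protocol shows it, and both groups meet the same surgical indication.
- A reader might attach a false-positive rate. For 50 versus 25 completers at two-sided 5%, a spurious difference of 0.2, 0.3 or 0.4 SD would give about 13%, 23% or 36%. Those rates hold for a comparison of levels with assumed inputs. They do not carry over to the group-by-time contrast, where a stable offset cancels; bias there requires the factor to modify the response to surgery.
- The regression on clinical characteristics is planned, and an analysis plan may add ANOVA covariates. So it would be wrong to say that nothing can correct the contrast later. As described, however, the regression does not adjust the group comparison.
- Incretin, cytokine and tissue samples are frozen for later analysis, so enrolment date need not determine assay date for these markers.
- An unselected consecutive group is a legitimate choice that favours representativeness.

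What remains is a non-randomised contrast with no comparability rule at enrolment, no adjusting term in the stated model, and a site imbalance fixed by the design.

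**Conclusion.** The point holds for the secondary T2DM versus non-DM contrasts and for the non-DM level of the three-group ANOVA. It does not reach the primary objective, which compares short- with long-standing T2DM and does not use the non-DM group.

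The only imbalance that the protocol itself demonstrates is site, 27% versus 50% from Graz. A difference in enrolment period follows from the stated volumes if recruitment is literally consecutive and participation is similar in both groups; it does not follow if non-DM participation is far lower. Confounding by age, sex or BMI is a reasonable possibility of unknown size. This is worth correcting because the remedy is cheap and its enrolment part is available only before recruitment, but it does not threaten the main result.

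**What to change.** **Section 6, Statistical analysis.** For the T2DM versus non-DM comparisons, add site, age, sex and baseline BMI as covariates, with their interactions with time where change is compared. These data are already collected. With 75 completers, three groups and four single-parameter covariates, 75 − 3 − 4 = 68 between-subject degrees of freedom remain.

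**Methodology, Population.** Keep consecutive recruitment for T2DM patients. Open non-DM places in step with T2DM enrolment at each site: one per two to three T2DM patients at St. Gallen (40/15 = 2.7) and one per T2DM patient at Graz (15/15 = 1). Fill them by frequency matching on sex, age band and baseline BMI band. This reduces differences in the matched factors and in enrolment period but does not remove them. Because it works within site, it leaves the Table 1 site imbalance in place, so the site term is still needed.

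**Cost.** A short addition to the recruitment rule and a recruitment log, with no extra patients or procedures. Non-DM enrolment finishes later, some willing non-DM patients are passed over, and the non-DM group becomes less typical of all non-diabetic bypass patients.
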